### 2.8. Effectiveness Outcome Measures

Preliminary effectiveness will be evaluated by measuring changes in several different outcomes, including care integration, information and service needs, parent/carer distress and child symptom burden, using validated measures described below. The schema for the timing of all measures is outlined in Table 4 and Table 5.

Paediatric Integrated Care Survey (PICS): A family-reported survey tool of experiences of care integration [33]. The scale comprises five subdimensions: access to care; communication between care team members and parents/guardians; assessment and remediation of the impact of the child’s healthcare needs on the family; creation of short- and long-term care goals, and team functioning and quality of the care team [34]. We will compare outcomes from a historical control group (*n* = 100), matched for child age and diagnosis as closely as possible.Information and Service Needs: A bespoke survey was developed to assess the specific components of the RECOVER model of care from the perspectives of parents. The 15-item survey was developed from literature and includes domains for information needs; timing; utility and usefulness; and knowledge and confidence (see Supplementary Materials).Caregiver Quality of Life Cancer (CQOLC): This quality of life scale is a validated and reliable measure, comprising 35 items on a 5-point Likert scale, which we have widely used in other studies with this population [35]. We will compare outcomes of a historical control group (*n* = 100), matched for child age and diagnosis, as closely as possible.Distress Thermometer for Parents (DT-P): The DT-P is a valid and reliable short screening tool for identifying parental distress in the context of a chronically ill child (0–18 years). The DT-P consists of a thermometer score from 0 (no distress) to 10 (extreme distress) and a problem list (practical, social, emotional, physical, cognitive, and parenting domains) [36]. We will compare outcomes from a historical control group (*n* = 100), matched for child age and diagnosis as closely as possibleChild Symptom Burden: Child symptoms are measured with the PROMIS paediatric proxy-item banks, which include domains for physical function, emotional distress, social peer relationships, fatigue and pain interference [22]. The measure is well validated and deemed clinically feasible and responsive in the paediatric cancer setting [37].

**Table 4 healthcare-13-00454-t004:** Implementation outcome measures mapped to the RE-AIM framework.

Outcomes	Data Collected	Timing
RE-AIM DOMAIN: REACH		
% of referrals to the RECOVER model of care among eligible children	Research nurse completes in database	Audit at the completion of recruitment
Clinical and demographic characteristics of referred patients	Child medical records	At recruitment
Acceptability, satisfaction, barriers, enablers	Semi-structured interview/survey with parents and healthcare professionals	At study completion
RE-AIM DOMAIN: EFFECTIVENESS		
Changes in experiences of integrated care between the historical control group and RECOVER sample over time	Paediatric Integrated Care Survey (PICS) [33]	Baseline, 6 and 12 months
Changes in parent/carer distress and QoL compared to the historical control group and over time	Distress Thermometer–Parent [36]	Baseline, 6 and 12 months
Changes in child symptom burden over time	PROMIS paediatric proxy-item bank [22]	Baseline, 1, 6, and 12 months
Changes in information and service needs over time	The 15-item survey was developed for the study	Baseline, 6 and 12 months
RE-AIM DOMAIN: ADOPTION AND MAINTENANCE		
% eligible children/caregivers/provided with Treatment Summary and Care Plan	Research nurse completes in database	Audit at the completion of recruitment
% aware of the RECOVER model of care	Semi-structured interview/survey with healthcare professionals	At study completion
Fidelity to protocol—elements of model of care completed	Research nurse completes in database	Audit at the completion of data collection
Number of interventions/referrals/recommendations made per patient	Research nurse completes in database	Audit at the completion of data collection
RE-AIM DOMAIN: IMPLEMENTATION		
Acceptability, Appropriateness	Semi-structured interview/Survey with parents and healthcare providers	Parents at 3-month follow-up. Healthcare providers at the completion of data collection
% of patients presented at MDT meetings, the composition of MDT	QCH/QOOL records	Direct observation
% of Documentation of Treatment Summary and Care Plan in iEMR and My Health Record	QCH records—Research nurse completes in database	Audit completion of data collection
% of Treatment Summaries/Care Plans shared with GP	QCH records-Research the nurse completes in the database	At the completion of data collection
Implementation Costs	Research nurse records time for clinical activities in the database, including health and needs assessment, MDT, preparation of documents and communication with clinical staff	Audit at the completion of data collection

QCH: Queensland Children Hospital, QoL: quality of life, MDT: multidisciplinary team, QOOL: MDT software, iEMR: Integrated Electronic Medical Record, GP: general practitioner.

**Table 5 healthcare-13-00454-t005:** Data collection schema.

Procedures	Pre-Enrolment	Baseline	1 Month	6 Months	12 Months
Eligibility Screening	X				
Recruitment	X				
Medical record review	X				X
Health and Needs Assessment		X			
Child Symptom Burden		X	X	X	X
Paediatric Integrated Care		X		X	X
Quality of Life—Parent		X		X	X
Distress Thermometer-Parent		X		X	X
Information and services needs			X	X	X
Exit interview/survey					X
In-depth interview (subset only)				X	X

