### 2.5. Procedures

Recruitment of parents of children with cancer: After active treatment, childhood cancer survivors will be stratified by clinical staff for risk of long-term and late effects according to validated protocols [26], identifying those who would benefit from early intervention and proactive management of the RECOVER model of care. While this process aims to identify those who would benefit most from the intervention, eligibility is broad, as outlined below, and children at lower risk are eligible if deemed clinically appropriate. As the model of care focuses on the transition from acute care services to community-based services, it is not suitable for children with uncertain prognosis, palliative care needs or other complexities. For these reasons, clinical staff review the suitability of all participants. Details of the parents of eligible children will be passed to the research nurse, who will provide written and verbal information and obtain informed consent to participate following standardised procedures [27]. We aim to recruit 40 parents.

Recruitment of healthcare professionals: Healthcare professionals (*n* ~ 10–15 medical, nursing, and allied health staff) involved in the care of children with cancer will be recruited through professional networks.

Study inclusion and exclusion criteria are presented in Table 3.

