Families’ psychosocial needs, including support for siblings and mental health, are crucial but often unmet. Families express a need for ongoing psychosocial support, particularly as the child reintegrates into normal life.	These discussions highlighted that while clinical treatment is paramount, emotional and psychological support for families should not be overlooked.
Survivorship care planning	
Ongoing challenges in how survivorship is managed, both in terms of the terminology used and the timing of the provision of care plans and follow-up services. Recognition there is a ‘grey area’ following the end of treatment. Families have voiced it would have been helpful to have had the connection to services without a large gap in continuity of care.	This reflects the uncertainty families experience in transitioning from active treatment to survivorship care, emphasising the need for a more structured, continuous approach to post-treatment planning.

**Table 3 healthcare-13-00454-t003:** Inclusion and exclusion criteria of the study.

Participants	Inclusion Criteria	Exclusion Criteria
Parents/carers of children treated for cancer	Child Any diagnosis of cancer; Aged 0–18 years at the time of diagnosis; Beginning surveillance or nearing the end of planned treatment or within two years of completion of treatment. Parent/carer Over 18 years; Able to read and understand English; Willing to freely provide informed consent and participate in study procedures;	Child/parents/carers deemed not suitable by clinical teams. Child with uncertain prognosis or palliative care needs.
Health professionals	Clinicians (doctors, nurses, and allied health professionals) who provide care through Queensland Health public hospitals; The participants’ nominated family general practitioner.	None; all clinicians who meet the inclusion criteria are eligible to participate.

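### No stated rule holds the historical controls to the eligibility criteria and treatment-phase window that RECOVER families must meet, so comparability of the two groups is not ensured

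*Protocol article*

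**What the plan says.** **RECOVER group.** Section 2.5 (Procedures) says the model is for the transition to community-based services, so "it is not suitable for children with uncertain prognosis, palliative care needs or other complexities", and that "clinical staff review the suitability of all participants". Table 3 makes these formal exclusions: "Child/parents/carers deemed not suitable by clinical teams. Child with uncertain prognosis or palliative care needs". Table 3 also sets a window: the child is starting surveillance, close to the end of planned treatment, or no more than two years past it. Risk stratification is described in section 2.5 as well ("childhood cancer survivors will be stratified by clinical staff for risk of long-term and late effects according to validated protocols"), but with the qualification that "eligibility is broad, as outlined below, and children at lower risk are eligible if deemed clinically appropriate".

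**Control group.** Section 2.4 says the controls come from a previous study under its own ethics approval. Section 2.8 describes their selection in almost the same words for PICS, CQOLC and DT-P: "We will compare outcomes from a historical control group (*n* = 100), matched for child age and diagnosis as closely as possible". Section 2.9.2 repeats the rule with age and cancer type. It adds regression for confounders where possible and names no covariates.

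**Limitations.** Section 3.4 lists voluntary participation, self-report and local context. It does not mention whether the historical controls are comparable.

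**The concern.** Who may serve as a control is part of the design. The article publishes detailed eligibility for one group and two matching variables for the other. Two children of the same age with the same tumour can differ in prognosis and in time since treatment, and matching on age and diagnosis balances neither.

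This matters for these outcomes. Two of the three historically controlled measures are parental distress and caregiver quality of life, and the Introduction itself says that caregivers' anxiety rises as treatment nears its end. If controls were assessed in another phase, or include families whom Table 3 would have kept out, part of any difference would reflect who was compared and not what the model did. Such a difference could be read as a preliminary efficacy signal, or could hide one.

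**Working it through.** The article gives no power, alpha, effect size or SD for this comparison, so there is no figure of its own to reproduce. The main check is to set the two selection rules side by side.

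| Criterion | RECOVER families | Historical controls |
|---|---|---|
| Child age and diagnosis | Age 0–18 at diagnosis, any cancer (Table 3) | Matched as closely as possible (2.8, 2.9.2) |
| Uncertain prognosis or palliative needs | Excluded (2.5, Table 3) | No rule stated |
| Suitability judged by clinical team | Required (2.5, Table 3) | No rule stated |
| Time relative to end of treatment | Nearing the end to two years after (Table 3) | No rule stated |
| Late-effects risk | Steers referral, not an exclusion (2.5) | No rule stated |
| Other confounders | Regression if possible, covariates not named (2.9.2) | Same |

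The three rows on prognosis, suitability and timing are firm on one side and open on the other.

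**How bias would arise.** Section 2.9.2 compares changes in outcomes. A control family with a steady excess of distress adds nothing to a change score, so the relevant quantity is a difference in mean change. If a share f of controls would fail Table 3, and their mean change differs by d (in SDs of the analysed score), the control mean is shifted by b = f × d. Both f and d are assumptions, because the documents give neither:
- f = 0.10, d = 0.5: b = 0.05 SD
- f = 0.20, d = 1.0: b = 0.20 SD
- f = 0.30, d = 1.0: b = 0.30 SD

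**What a given bias would do.** Inputs: 40 RECOVER parents (2.5), 100 controls (2.8), common SD, no true effect, two-sided alpha 0.05 (assumed), normal approximation.
- SE = √(1/100 + 1/40) = √0.035 = 0.187 SD.
- Difference detectable with 80% power = (1.960 + 0.842) × 0.187 = 0.52 SD.
- False-positive rate = 1 − Φ(1.96 − b/SE) + Φ(−1.96 − b/SE).

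| Bias b (SD) | 40 vs 100 | 40 vs 40 (SE = √(1/40 + 1/40) = 0.224) |
|---|---|---|
| 0 | 5% | 5% |
| 0.1 | 8% | 7% |
| 0.2 | 19% | 15% |
| 0.3 | 36% | 27% |

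The last column covers one-to-one matching, with the groups treated as independent; the article gives no matching ratio.

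**What restricting the controls would cost in precision.** With 90 controls left, SE = √(1/90 + 1/40) = 0.190. With 70 left, SE = √(1/70 + 1/40) = 0.198. Against 0.187, these are increases of about 2% and 6%. The RECOVER sample of 40 dominates the standard error, so losing some controls costs little.

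**The case against.** The strongest reply is that the earlier study may have recruited end-of-treatment families and excluded palliative cases itself. Its criteria are not shown, and a condensed article may leave them to the full protocol. This stands in part. A reader might infer that the two groups are drawn from different eligible populations, or that relapsed or palliative families sit among the controls. The article supports neither statement; it shows only that no stated rule prevents this.

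A reader might also infer that RECOVER families are selected by late-effects risk, from the words "identifying those who would benefit from early intervention and proactive management of the RECOVER model of care". The sentence that follows says eligibility is broad and includes lower-risk children, and Table 3 has no risk criterion. Stratification may influence who is referred, but it is not an entry filter.

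A third tempting step is to put a figure in DT-P points on the bias and call it favourable to RECOVER. The documents do not support this. The planned comparison is of changes, so an excess in level may cancel. The possible influences also need not act in one direction: keeping poor-prognosis families out of one side only could flatter RECOVER, while steering higher-risk children into it could do the opposite.

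The conditional regression in section 2.9.2 is a real safeguard and is not limited to age and diagnosis. But it may not be done, it names no covariates, and it cannot adjust by data for a kind of family that is absent from the RECOVER side. Restriction is the remedy for that.

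Finally, feasibility and acceptability are the primary objectives, and the control comparison is presented as preliminary in an openly non-randomised study. That limits the weight of the point but does not remove it.

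**Conclusion.** The point holds in this form: Table 3 restricts RECOVER families by prognosis, palliative need, clinician-judged suitability and time relative to treatment completion. The only stated selection of controls is matching on child age and diagnosis, and adjustment is optional and unspecified. Comparability is not ensured, and section 3.4 does not say so.

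The size and direction of any bias are unknown. The false-positive rates above rest on assumed bias values and an assumed 5% test; they show only that a bias well below the roughly 0.52 SD detectable difference would matter. If the earlier study used equivalent criteria and timing, the bias from this source could be close to nil. The change is worth making because it is cheap and affects a secondary comparison that will be read as evidence of effect.

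**What to change.** 1. State the earlier study's eligibility criteria and when its families were assessed relative to treatment completion.
2. Before matching, restrict the controls to those meeting the Table 3 criteria that existing records can establish: no palliative needs or uncertain prognosis, and time relative to treatment completion. Use only control assessments from the same window.
3. Keep matching on child age and diagnosis. Name time since treatment completion, and late-effects risk stratum where available, as adjustment covariates. A third matching variable could leave poor matches for 40 families from at most 100 controls.
4. Restate how many of the 100 controls remain.
5. Add to section 3.4 that clinician-judged suitability cannot be recreated retrospectively, so some selection difference may persist.

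Cost: a check of existing data on at most 100 families, a reworded control definition, and possibly fewer usable controls. Feasibility depends on what the earlier study recorded and on its permissions, which the article does not describe. If its criteria already match, few or no controls are lost.

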### 2.4. Implementation and Effectiveness Evaluation

A prospective consecutive group of child cancer patients and their parents will be recruited as the patients transition to the end of active treatment and surveillance to receive the RECOVER model of care. Data will be collected over 18 months to evaluate the immediate and longer-term impacts on carers’ information needs and experiences of integrated care. An embedded health services evaluation, informed by implementation science, will establish the feasibility, acceptability, impact, and value of the RECOVER model of care. This systems-level approach assesses processes, outcomes, and costs of interventions [24]. The study outcomes will be reported in peer-reviewed journals according to the Strengthening and Reporting of Observational Studies in Epidemiology Statement [25].

Study design: A Type 2 Hybrid Implementation/Effectiveness non-randomised controlled study design will be used to compare data from a historical control group (collected in a previous study, HREC/19/QCHQ/53816) with a prospectively recruited group of carers in the current study. Evaluation will focus on the implementation and preliminary efficacy of the model of care from the perspectives of patients/carers and the health service.

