### 2.6. Data Collection

Parents: After providing consent, the participant will complete baseline measures. They will then receive the RECOVER model of care intervention as described above. Data will be collected to assess outcomes at three time points; Table 4 and Table 5. Semi-structured interviews will be completed with participants at follow-up to ascertain their feedback on acceptability and satisfaction with the model of care. Interviews will be completed by trained and experienced research staff and audio-recorded and transcribed verbatim.

Healthcare professionals: Interviews and/or surveys will be conducted with clinical staff to determine acceptability, satisfaction, barriers, and enablers for the model of care. Interview guides/surveys for healthcare professionals focus on implementation factors and are informed by domains from the PARiHS framework [28] to assess the local, organisational, and external contexts.

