### 2.7. Measures and Outcomes

Implementation outcomes: Implementation evaluation is informed by Proctor’s implementation outcomes [29], and mapped to the RE-AIM [30] implementation framework (Table 3) and include the following:Feasibility and adoption assessed through (1) enrolment rates (proportion of eligible children’s parents who are (i) referred and (ii) consent to participate) defined a priori as greater than 50% of eligible parents enrolling in the model of care intervention [31]. (2) Proportion of enrolled participants provided with (i) Treatment Summary and (ii) Surveillance Care Plan. (3) Qualitative feedback mapped.Acceptability and appropriateness explored through (1) Rates of survey completion by parents at all times; considered acceptable if at least 70% of parents complete surveys [32]. (2) Parent/carer and health professional qualitative data collected through interviews. Parents will be asked about their satisfaction with the process, the relevance of collecting survey data, and the usefulness of the Treatment Summary and Surveillance Care Plan. Health professionals, including the family’s GP, will be asked about their satisfaction with the RECOVER model of care process and its relevance to clinical practice.Implementation Cost estimates will be based on the time the RECOVER Clinical nurse spends on clinical activities. The time spent will be prospectively recorded in a REDCap database during key activities, including review of medical records, development of Treatment Summary and Surveillance Care Plan, direct parent/child contact, preparation and attendance at MDT meetings, documentation and follow-up review. Monetary costs will be calculated using the 2024 wage rates for a Queensland Health Clinical Nurse with an additional 25% added to account for on-costs.Fidelity and Penetration will be assessed by an audit of the elements of the model of care completed for each child patient and fidelity to protocol as documented by the research nurse in the study database.

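### Delivery of the Treatment Summary and Care Plan has two conflicting denominators (enrolled in section 2.7, eligible in Table 4), and Table 4 audits it at a point when the latest recruits may not yet have been served

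*Protocol article*

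**What the plan says.** Section 2.7 (Measures and Outcomes), under feasibility and adoption, lists delivery of the two documents as "Proportion of enrolled participants provided with (i) Treatment Summary and (ii) Surveillance Care Plan". The item before it is the enrolment rate, whose success criterion is "defined a priori as greater than 50% of eligible parents enrolling in the model of care intervention". The section says its outcomes are mapped to RE-AIM.

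Table 4, in the adoption and maintenance domain, has a row for the percentage of "eligible children/caregivers/provided with Treatment Summary and Care Plan", timed as "Audit at the completion of recruitment". In the same domain, the rows for fidelity and for the number of referrals are timed as "Audit at the completion of data collection". In the implementation domain, filing of the documents in the electronic record and sharing them with the GP are also audited once data collection is complete.

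Section 2.6 puts consent and baseline measures first and says of participants: "They will then receive the RECOVER model of care intervention as described above". Section 2.2 describes that intervention in seven steps. The documents are provided to the family in the last one, after the needs assessment, the MDT presentation, preparation of both documents, oncologist approval and a clinical review.

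The recruitment target in section 2.5 is "We aim to recruit 40 parents". Section 2.4 says "Data will be collected over 18 months", and Table 5 places the last survey at 12 months. The article gives neither the length of recruitment nor the expected time from consent to delivery.

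**The concern.** Enrolled and eligible are different populations in this protocol, because section 2.7 defines one as a proportion of the other. A percentage of enrolled families says how completely the service reached those who consented. A percentage of eligible families also carries non-enrolment, which the preceding item already measures. Feasibility is a primary objective, and these two documents are the main product of the model. The analysis in section 2.9.1 is descriptive, so the proportion reported is itself the result. With both definitions available, the choice could be made after the data are seen.

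The audit time is a separate problem in the same row. Closing recruitment is a sensible moment to count referrals, which Table 4 times in the same way. It is a doubtful moment to count documents that reach a family only after several steps following consent. In section 2.2, giving the documents to the family, sending them to health professionals and uploading them all belong to the final step. Table 4 nevertheless audits the first of these earlier than the other two. The table could therefore show more documents filed than provided.

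**Working it through.** The article states no expected delivery rate, so there is no figure to reproduce.

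**Denominator.** Let e = enrolled/eligible and d = the share of enrolled families given the documents.

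- Section 2.7 figure = d.
- Table 4 figure = d × e, assuming that eligible families who do not enrol receive no documents.
- Ratio = d / (d × e) = 1/e, whatever d is.

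With 40 enrolled (section 2.5) and all served (d = 1):

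| e | Eligible (40/e) | Section 2.7 figure | Table 4 figure | Ratio |
|---|---|---|---|---|
| 40% | 100 | 100% | 40% | 2.50 |
| 50% (threshold) | 80 | 100% | 50% | 2.00 |
| 60% | 66.7 | 100% | 60% | 1.67 |
| 70% | 57.1 | 100% | 70% | 1.43 |
| 80% | 50 | 100% | 80% | 1.25 |
| 100% | 40 | 100% | 100% | 1.00 |

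The eligible counts are derived from e and are not in the protocol. If a share u of non-enrolled families did receive documents, the Table 4 figure would be d × e + u × (1 − e). The gap would then narrow, and it would vanish at u = d.

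**Audit time.** Assume uniform accrual of 40 families over T months and a lag of L months from consent to delivery. The share of enrolled families not yet served when recruitment closes is L/T. Per eligible family it is e × L/T. Neither T nor L is stated, so both are shown over a range. T = 6 is what 18 months of data collection less 12 months of follow-up would imply, if the 18 months covers both.

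| L (months) | T = 6 | T = 12 | T = 18 |
|---|---|---|---|
| 0.5 | 3.3 families (8%) | 1.7 (4%) | 1.1 (3%) |
| 1 | 6.7 (17%) | 3.3 (8%) | 2.2 (6%) |
| 3 | 20 (50%) | 10 (25%) | 6.7 (17%) |

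These percentages are of the 40 enrolled. The Table 4 row is per eligible family, so at e = 50% each is halved. For L = 1 the loss is 6.7/80 = 8, 3.3/80 = 4 and 2.2/80 = 3 percentage points.

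**Both together.** At e = 50%, L = 1 and T = 6, the Table 4 figure at the close of recruitment is at most (40 − 6.7)/80 = 42%. The section 2.7 figure after complete delivery is 100%.

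**The case against.** The case against is strongest on timing. An audit at the completion of recruitment says when the database is reviewed. It sets no data cut-off and no rule that pending families count as not provided, and it could be run late enough to include them. Table 3 admits families up to two years after treatment ends, so not every late recruit is waiting for treatment to finish. The fidelity, filing and GP-sharing audits come later and record steps involving the same documents, so late delivery would not stay hidden. All of this stands. It makes the timing point a conditional one, but it does not explain why this row alone among the document audits is timed early.

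Three stronger readings are tempting and are not supported:

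- A reader might infer that the adoption figure will be out two-fold. That is the boundary case. The criterion is enrolment above 50%, so the ratio is below 2 whenever the criterion is met, and smaller still if non-enrolled families receive documents. The two-fold gap comes from the denominator alone.
- A reader might infer that each month of lag costs 17 percentage points of the Table 4 figure. That applies section 2.7's denominator to Table 4's audit date. On the eligible denominator it is about 8 points, and then only for a 6-month accrual at 50% enrolment.
- A reader might infer that the early audit biases both figures. Section 2.7 gives no audit time, so its figure is affected only if Table 4's timing is applied to it.

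It is also fair to say that delivery has no success threshold, test or sample-size role. The two rows could serve as different measures, but the article does not label them so.

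**Conclusion.** The denominator conflict is explicit in the text and unresolved. If only enrolled families receive the documents, the two definitions differ by 1/enrolment rate: 2.0 at 50%, 1.43 at 70% and 1.25 at 80%. The assumption fits section 2.7, which speaks of parents enrolling in the intervention itself, but the article does not state it outright.

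The audit time may produce an undercount under a literal reading. Its size rests on uniform accrual and on an accrual period and lag that the article does not give. For a one-month lag it ranges from about 17% of enrolled families (6-month accrual) to 6% (18-month accrual), or half that per eligible family at 50% enrolment. The later audits would partly expose it.

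What is affected is a reported descriptive figure under a primary objective. No hypothesis test, sample size or success criterion depends on it. The correction is worth making because it is cheap and removes a choice that could otherwise be made after the results are known.

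**What to change.** State the same denominator for document delivery in section 2.7 and Table 4. Alternatively, report both as separately labelled measures, provided/eligible and provided/enrolled, with the counts shown. Neither should be called fidelity, because section 2.7 and Table 4 already use that term for the audit of model elements completed.

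Move the delivery audit to the completion of data collection, in line with the fidelity, filing and GP-sharing rows, or fix it at a set interval after each family's consent.

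The cost is a change of wording and a later database query. The research nurse already records delivery, and the number eligible is already needed for the enrolment rate, so no new data are required.

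### Tables 4 and 5 give incompatible schedules for the Information and Service Needs survey; under Table 5 this change outcome has no pre-intervention value

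*Protocol article*

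**What the plan says.** Section 2.8 describes a survey written for this study, with "domains for information needs; timing; utility and usefulness; and knowledge and confidence". Table 4 places it in the effectiveness domain of RE-AIM. The outcome there is "Changes in information and service needs over time", the instrument entry is "The 15-item survey was developed for the study", and the timing is "Baseline, 6 and 12 months".

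Table 5, the data collection schema, lists the same survey as "Information and services needs". That row is marked at 1, 6 and 12 months; the pre-enrolment and baseline cells are empty.

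Section 2.8 sends the reader to both tables for the timing of all measures and does not say which one governs. Section 2.6 fixes the order of events: "After providing consent, the participant will complete baseline measures. They will then receive the RECOVER model of care intervention as described above". It adds: "Data will be collected to assess outcomes at three time points; Table 4 and Table 5".

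Section 2.4 says the data will serve to evaluate immediate and longer-term impacts on carers' "information needs and experiences of integrated care". The aims at the end of the Introduction also name caregiver information needs among the outcomes on which impact will be assessed.

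**The concern.** A change outcome needs a starting value. With historical controls, a missing baseline might be partly made good by comparing levels between groups. For this survey no such comparison is named: section 2.8 names the historical group for the integrated care survey, the caregiver quality-of-life scale and the distress thermometer only. The within-parent contrast is therefore the only one stated for it, and that contrast depends on whether the first administration comes before or after RECOVER begins.

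The two tables answer that question differently. If the study team works from the Table 5 schema, every score on this instrument is taken after the baseline visit. The analysis would then describe how needs move after 1 month, and not how far the model of care shifted them from their starting point. A baseline that was not collected cannot be recovered for parents already enrolled.

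**Working it through.** The document states no sample-size calculation, effect size or variance for this outcome, so there is no figure of the plan's own to reproduce. The check is a comparison of the two schedules, followed by a short piece of algebra.

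**Step 1. The schedules side by side.**

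| Measure | Table 4 | Table 5 |
|---|---|---|
| Integrated care survey | baseline, 6, 12 | baseline, 6, 12 |
| Distress thermometer | baseline, 6, 12 | baseline, 6, 12 |
| Child symptom burden | baseline, 1, 6, 12 | baseline, 1, 6, 12 |
| Information and service needs | baseline, 6, 12 | 1, 6, 12 |

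Three of the four measures agree in the two tables. Only the information-needs survey differs.

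**Step 2. Is this a fault of text extraction?** In Table 5 the child symptom burden row has two separators before its first mark, which puts that mark under baseline. The information-needs row has three, which puts its first mark under 1 month. All rows fit the same column header, so the empty baseline cell is real.

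**Step 3. Does other text settle it?** Section 2.6 speaks of three time points, but each table gives three for this survey, so the count does not choose between them. Section 2.8 cites both tables with equal standing.

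**Step 4. Contrasts available under each schedule.**
- Common to both tables: 6 and 12 months.
- Under Table 4: baseline to 6 and baseline to 12 months; no 1-month value.
- Under Table 5: 1 to 6, 1 to 12 and 6 to 12 months; none starts from a pre-intervention value, because section 2.6 places the intervention after the baseline measures.

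**Step 5. What the Table 5 contrast would show.** Let D be the lasting fall in unmet need, and f the share of D already reached by the 1-month survey. Assume the full fall is present at 12 months.
- Baseline to 12 months: change = −D.
- 1 to 12 months: change = −D − (−fD) = −(1 − f)D.

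The document does not give f, so it is shown over its range, with a hypothetical D of 1 SD:

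| f (assumed) | Baseline to 12 months | 1 to 12 months |
|---|---|---|
| 0 | −1 SD | −1 SD |
| 0.5 | −1 SD | −0.5 SD |
| 1 | −1 SD | 0 |

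The earlier the model takes effect, the less of that effect Table 5 can show. The value of 1 SD is an illustration and not an estimate.

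**Step 6. Is there another baseline?** Section 2.2 describes a Health and Needs Assessment that covers unmet information needs, and Table 5 marks it at baseline. It has its own row, is not marked again at follow-up, is itself a step of the model of care, and is not stated to contain the 15-item survey. It may describe needs at the start, but it yields no change score on the outcome's instrument.

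**The case against.** The strongest reply is that the document shows an ambiguity and not a lost baseline. Table 4 has the same standing as Table 5, and a mark left out of the schema by oversight is an equally possible reading. This stands. A reader might infer that the pre-intervention value is missing for all 40 parents; the document supports that only on the condition that Table 5 is what is carried out.

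Second, the Abstract makes feasibility and acceptability the primary objectives and places preliminary efficacy among the secondary ones. This also stands. A reader might take the outcome as central because information needs come first in the list of impact outcomes in the Introduction, but order in a list does not make an outcome primary, and no primary conclusion depends on this survey.

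Third, 1 month need not fall after the benefit. Section 2.2 sets no deadline for the team presentation, the treatment summary, the care plan or the clinical review, so the 1-month survey may fall during delivery. This is fair, and it is why f is left free above. It reduces the possible distortion but does not supply a pre-intervention score.

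Fourth, items on the usefulness of RECOVER components cannot sensibly be answered before a family has received them, which may explain the empty cell. That is plausible, but it leaves the baseline entry in Table 4 wrong for those items, so the tables still have to be reconciled. Nor can the split of items be settled here, since the survey is in supplementary material that is not shown.

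Fifth, other evidence on information needs exists in the Health and Needs Assessment and the interviews. It is useful context, but no change score from either is described.

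**Conclusion.** The contradiction is established from the document alone: baseline, 6 and 12 months in one table, and 1, 6 and 12 months in the other, for the same instrument with no rule of precedence.

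Its consequence is conditional. If Table 5 is followed, the number of parents with a pre-intervention score on this survey is 0 of the planned 40, and an early, sustained benefit could appear as anything down to no change. If Table 4 is followed, change from baseline is available at 6 and 12 months, but nothing is measured on this survey before 6 months, which sits poorly with the immediate impact that section 2.4 sets out to evaluate.

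Severity is moderate: the outcome is secondary, but it is a named aim with no stated historical comparator. The conclusion assumes that the unseen Health and Needs Assessment does not embed the survey, and that the general sentence on historical controls in section 2.9.2 does not extend to an instrument developed for this study. A finding that the trial cannot assess information needs at all would go beyond what the document shows.

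**What to change.** Make the two tables agree:

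- In Table 5, mark a baseline administration, placed before the Health and Needs Assessment and any other RECOVER contact, of the survey items that can be answered before the intervention. By their labels these are the information-needs and the knowledge and confidence domains; confirm this against the instrument.
- In both tables, state whether a 1-month administration occurs.
- Where the remaining items, such as those on utility, are given only after the intervention, say so in both tables.
- Define the outcome as change from baseline on the items common to all time points, so that a shorter baseline form is not compared with a longer follow-up total.

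The cost is a few more items at a visit that already takes place, with slight extra burden for parents, and a short amendment to both tables. If recruitment has begun, report how many parents completed the survey at baseline and at 1 month, and which schedule was used for them.
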